### Secondary outcomes

The secondary outcomes in this study are conceptualized as (a) children’s cognitive-emotional processes that are essential for children’s mental health and efficient social skills, and (b) contextual factors (e.g. home and school) that are known to contribute to the well-being and social development of children. Children’s socio-cognitive processes are assessed with computer based tasks on emotional understanding, altruistic behavior, and executive functions. The teacher and principal rated secondary outcome measures include e.g. school environment, teacher self-efficacy and emotional self-efficacy, child rearing practices, and teacher-parent collaboration. The parent rated secondary outcome measures include e.g. emotional self-efficacy, child rearing practices, and teacher-parent collaboration.

*The Children’s secondary outcomes* were assessed with the Assessment of Children’s Emotion Skills ACES; e.g. [25] measuring children’s ability to understand and recognize emotions in social situations, and with the child faces subtask of Diagnostic Analysis of Nonverbal Accuracy DANVA 2-CF; [26] measuring children’s ability to recognize facial expressions of emotions. The Dictator Game e.g. [27] was used to assess children’s other regarding preferences, i.e. behavioral tendency to share resources with others in a fair or selfish manner (e.g. altruistic behavior). Children’s executive functions were included as secondary outcomes as research suggest that they are important underlying mechanisms regarding emotion regulation and social competence e.g. [28, 29]. Executive functions were assessed with three cognitive tasks measuring working memory, ability to plan and solve problems, and inhibition, which were all adapted, created and computerized for the purposes of the present study. Working memory was assessed with a task similar to Corsi Block [30, 31] and children’s ability to plan and solve problems was assessed with a task similar to Tower of London [32–34]. Inhibitory control was assessed with a Go/No-Go –task [35, 36] using the same stimulus materials and parameters as in Vuontela and colleagues [37]. To complement parent and teacher ratings of children’s mental health, the children’s depressive symptoms were measured using Children’s Depression Inventory CDI; [38, 39].

*Teacher rated secondary outcomes* concerning *stress and work engagement* were measured using the Single Item Stress Index [40], the Bergen Burnout Inventory [41] and the Utrecht Work Engagement Scale UWES; [42, 43]. Secondary outcome measures for *self-efficacy* were the Teachers’ Sense of Efficacy Scale TSES; [44], Perceived Collective Teacher Efficacy [45], and Teacher SEL Beliefs Scale [46]
*. The school environment and leadership* were measured with the Revised- School Level Environment Questionnaire R-SLEQ; [47], see also [48] and the Global Transformational leadership scale GTL; [49]. *Teacher-parent collaboration* was measured with the shortened version of the Trust scale [50] and Family-professional Partnership Scale [51], which has been tested and used in prior Finnish studies e.g. [52]. *Teacher-child interaction* was measured with a Finnish version of the revised Child Rearing Practices Report Scale CRPR; [53] and Psychological Control Scale [54]. These measures have also been tested and used in related Finnish studies (both in school and home environments) and are referred to as teaching style and parenting style [55–57]. Finally, teachers’ own *socio-emotional skills* were measured with the Emotional Self-Efficacy Scale ESES; [58]. Teacher related outcomes were deemed to be interesting and important because of their potential mediating role regarding the intervention effectiveness as a whole. In line with the whole school approach, work community measures were also included, such as school environment and leadership, which have been shown to be important components of effective interventions.

*Parent rated secondary outcome measures* were partly the same as the teachers. The parents also completed the shortened version of the Trust scale and Family-professional Partnership Scale measuring parent-teacher collaboration. The same Finnish version of the revised Child Rearing Practices Report Scale was used for the parental interaction with their child (parenting style). Furthermore, parents’ own socio-emotional skills were also measured with the Emotional Self-Efficacy Scale in the same way as for the teachers. These measures were selected because of their potential mediating effect in promoting children’s socio-emotional skills.

### Data collection procedure

The data was obtained via electronic questionnaires (for the teachers and the parents) and computer based tasks and questions (for the children) as outlined in Table 2. For the parents’ there was also a paper version available. In addition to Finnish and Swedish, an abbreviated version of the parents’ questionnaire was available in English, Estonian, Russian, Somali, Albanian, Arabic and Chinese (the most frequent foreign languages in Finland and in the study schools). The parents’ foreign language questionnaires were paper versions and included only the background information and the SDQ.

Both the electronic questionnaires and children’s tasks intended for children who could not yet read were implemented with HTML5 and client-side Web technologies to be run remotely within an internet browser. Task implementation was iterated repeatedly by experts in web design, interactive technology, and psychology. Computerizing the original tests to perform robustly in varying internet browser, connection and technology environments turned out to be a significant, but doable challenge. All these technical assessments and the electronic data collection procedure were developed and executed by the Tampere Unit for Computer-Human Interaction (TAUCHI) unit from the School of Information Sciences at the University of Tampere in close collaboration with the intervention research team. The TAUCHI unit was responsible for the design and development of the electronic questionnaires and computerized tasks and provided technical input and expertise when needed.

The children’s computer based tasks and questionnaires included short practice tasks with animated and narrated instructions. The tasks were piloted to ensure that the children could master the tasks as independently as possible, without the help of the teacher at the time of the assessment. The children received both auditory and literal instructions to ensure that even the youngest children who could not read yet were able to understand the directions of the tasks.

The researchers had prepared guidelines and detailed material to help the teachers with their task as they would be carrying out and supervising the children’s assessments in their own schools. Furthermore, assistance was organized in case the teachers had trouble with managing this task on their own. In addition, the research group offered help and assistance to the teachers and parents during the whole data collection period via phone or email when needed.

The baseline data regarding the children was collected in four waves and from multiple sources, i.e. from the children themselves, their parents and teachers as outlined in Table 1. The baseline data collection started with the teacher and principal questionnaire in spring 2013 (T_0_) regarding their own work and the school environment. This was followed by the children’s assessments starting in the beginning of the autumn term 2013 (T_0_). The baseline data collection process ended with the teachers’ and parents’ evaluation on their child/children during autumn 2013 (T_0_). The teacher’s questionnaire, along with the evaluation of the child was sent via email with a personal password. The parental questionnaire was sent via email or mail. The teachers and parents were contacted first by email and then by phone if they had not completed the questionnaires or administered the children’s assessments within the required timeframe. The same procedure was replicated during spring 2014 when the T_1_ data was collected, and will be replicated also in spring 2015 during the T_2_ data collection.

The estimated completion time for various assessments and questionnaires were as follows: 40 minutes for the children’s assessment, 20 minutes for the parents’ questionnaire, 10 minutes for the teachers’ questionnaire regarding the child, and 20 minutes for the teacher’s and principal’s questionnaires regarding their own work and the school environment. The children were offered a small token (a sticker at baseline and a ruler at T_1_) after finishing the computer based tasks and questionnaires as a thank you and reward for their participation.

### Plan of statistical methods

Because of a clustered data structure, random effects linear regression models are applied to compare the means for continuous outcomes between the trial arms and generalized linear mixed models or generalized estimating evaluation (GEE) models to compare binary outcomes (e.g. borderline/abnormal versus normal status on the SDQ). Analyses are adjusted for important prognostic factors e.g. child gender, year group, and a baseline SDQ score. Stratified analyses according to year group will be performed.

The dataset will be preprocessed prior to the analysis and missing data will be handled properly. Imputation techniques will be used when necessary. Demographic and baseline characteristics will be summarized using means and standard deviations (or medians and inter-quartile ranges) for quantitative variables and percentages for categorical variables. Possible differences in the intervention effects between subgroups will be investigated in secondary analysis. These subgroups are formed based on SDQ scores and family socio-economic status.

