The intervention program Together at school will be evaluated in a cluster randomized trial (RCT). The aim of the trial is to compare the Together at School intervention group with the control group to evaluate the effectiveness of the intervention program in a whole school context. The control group school teachers participated in two general lectures regarding socio-emotional skills in child development. The aims of the evaluation study are to: 1) Evaluate whether the newly developed whole school intervention program improves mental health and social skills among primary school children. 2) To examine the influence of the intervention program on school environment (e.g. teaching style, collaboration with parents) and children’s emotional-cognitive processes (e.g. emotional understanding, executive functions), and to test whether these secondary outcomes mediate the effectiveness of the intervention. 3) To examine the role of potential moderator factors influencing the effectiveness of the intervention, such as children’s initially poor executive functioning and low socio-economic status. 4) To evaluate certain feasibility aspects (e.g. recruitment attainment, drop-outs, data collection agreements) of the large scale implementation. The aim of this paper is to describe a study protocol of a cluster randomized controlled trial.

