### Sample size

Power analyses were conducted to estimate the required sample size. The starting point for calculations was a multilevel model comprising two levels: school and pupil. It was assumed that 2-5 classes (typically 2-3) would participate per school, one class containing 20 pupils, the recruitment rate being 70% and attrition 10% during the follow-up. Calculations based on these assumptions resulted in a total of 25 (2*20*0.7*0.9) to 63 (5*20*0.7*0.9) children per school. The intra-cluster correlation coefficient (ICC) between schools for the primary outcome measure (SDQ total difficulties score) was assumed to be 0.15 [13] and the effect size between the intervention and control groups was expected to be a) 0.25 or b) 0.3. This is in line with corresponding research where the effect size has been found to vary between small and moderate [4, 9]. In a two level design using a significance level of 0.05 and requiring 80% power a sample size of a) 2400-5355 children (i.e. 96-85 schools) or b) 1675-3780 children (i.e. 67-60 schools) is required. Based on these calculations we decided to recruit 100 schools into the study. Sample size calculations were undertaken using Optimal Design Software [14].

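### Moderation by SDQ is planned through subgroups of a many-valued score; a treatment-by-continuous-baseline-SDQ interaction would be a cheap and, if modification is roughly linear, more efficient secondary test

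*Protocol article*

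**What the plan says.** All but the last two of these statements are in the Protocol article, Plan of statistical methods.

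- On effect modification: "Possible differences in the intervention effects between subgroups will be investigated in secondary analysis".
- On how the groups arise: "These subgroups are formed based on SDQ scores and family socio-economic status".
- On the outcome models, which for continuous outcomes are random-effects linear regressions: "Analyses are adjusted for important prognostic factors e.g. child gender, year group, and a baseline SDQ score".
- The only SDQ categories named are in "borderline/abnormal versus normal status on the SDQ". They are given as an example of a binary outcome, not as the cut for the subgroups.
- In the Background, aim 3 is "To examine the role of potential moderator factors influencing the effectiveness of the intervention", with the examples "such as children’s initially poor executive functioning and low socio-economic status".
- The Sample size section covers the main effect only.

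The article gives no cut-point, number of groups, informant or form of test for the SDQ subgroups. It also does not say in so many words that the grouping score is the baseline one, though that is the natural reading.

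**The concern.** Forming groups from a score treats all children within a group as alike and children just either side of the boundary as different. When the treatment effect changes gradually with the score, the contrast between groups uses only part of the information on that change. The article gives no reason for grouping, and the ungrouped score is already in the model.

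The efficiency of this analysis matters because the trial is sized for an average effect only: "the effect size between the intervention and control groups was expected to be a) 0.25 or b) 0.3". A gradient in that effect is likely to be small too, and no power is claimed for detecting one. If a gradient exists, a group comparison has less chance of showing it than the same data allow.

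The point is confined to the SDQ. The article does not say how family socio-economic status is scored, and that measure may be categorical by nature.

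**Working it through.** **1. The plan's own figures (main effect).** Inputs from Sample size: effect size d = 0.25 or 0.30, ICC 0.15, n = 25 or 63 children per school, and "using a significance level of 0.05 and requiring 80% power" (two-sided testing assumed). With J schools, the noncentrality is d / √(4(0.15 + 0.85/n)/J), referred to a noncentral t with J − 2 df.

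| d | n | Schools stated | Schools recomputed | Power at stated number |
|---|---|---|---|---|
| 0.25 | 25 | 96 | 95 | 0.807 |
| 0.25 | 63 | 85 | 85 | 0.804 |
| 0.30 | 25 | 67 | 67 | 0.805 |
| 0.30 | 63 | 60 | 60 | 0.807 |

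The stated sizes reproduce. None of them concerns an interaction.

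**2. Information kept by one cut.** Assumptions: normal score, linear modification, share p of children above the cut. The share of information kept is r² = φ(z)²/(p(1 − p)), where z is the cut on the standard normal scale.

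- Median, p = 0.5: 0.3989²/0.25 = 0.637, r = 0.798.
- Top 20%, p = 0.2: 0.2800²/0.16 = 0.490, r = 0.700.
- By the same formula: top third 0.595, top quarter 0.539, top 10% 0.342.

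**3. Effect on power.** Assume the continuous interaction test has 80% power, so its noncentrality is 1.960 + 0.842 = 2.802. After the cut, power is Φ(2.802r − 1.960).

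- Median: Φ(2.235 − 1.960) = 60.8%, a loss of 19 points.
- Top 20%: Φ(1.961 − 1.960) = 50.0%, a loss of 30 points.
- Top 10%: 37.4%, a loss of 43 points.
- Ordered tertiles fitted as a trend (r = 0.890): 70.3%, a loss of 10 points.

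**4. Dependence on the starting power.** Loss in points:

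| Power of continuous test | Median split | Top 20% |
|---|---|---|
| 30% | 9 | 13 |
| 50% | 15 | 22 |
| 80% | 19 | 30 |
| 95% | 13 | 24 |
| 99% | 6 | 14 |

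**5. At sizes near this trial's.** Take a child-level interaction with SE = √(4 × 0.85/N) and an assumed slope b, in SD of outcome per SD of SDQ. N = 2400 is the article's lowest planning total for d = 0.25; 3990 is the n it gives for parental consent.

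| N | b | Continuous | Median split | Top 20% |
|---|---|---|---|---|
| 2400 | 0.05 | 26.4% | 18.4% | 15.1% |
| 2400 | 0.10 | 75.7% | 56.4% | 46.0% |
| 3990 | 0.15 | 99.9% | 98.4% | 94.9% |

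**6. Simulation with clustering.** There were 1,500 simulated trials per gradient, with 79 schools of 45 children (assumed, within 25 to 63), ICC 0.15, an assumed slope of 0.6 of outcome on baseline, and a linear gradient of 0.08. Both split models also adjusted for the continuous score. Power was 83% continuous, 63% median split and 50% top 20%. With no gradient, rejection rates were 4.5% to 4.7% for all three. The loss therefore comes from the cut, not from a dropped covariate.

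**7. Departures from the assumptions.**

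- Skewed, SDQ-like score (assumed mean 7, SD 5.5), starting from 80%: power is 53% with a cut near the median, 61% with about the upper 20%, and 57% with about the upper 10%. The loss is 19 to 27 points, and the median split is now the worst of the three.
- True step at the cut: the ranking reverses. If the correct cut has 80% power, the linear term has 61% (step at the median) or 50% (step at the top 20%).

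**The case against.** **The article does not exclude a continuous test.** A reader might infer that the subgroup comparison replaces a treatment-by-continuous-SDQ interaction. The text does not go that far: it states no test and rules nothing out. Cut-points and the form of test are commonly left to a full protocol or SAP, and neither is shown, so their absence is no fault here. This stands. What remains is that grouping is the only approach described for moderation by SDQ, and a later document that merely set a cut would not recover the information lost.

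**No single power loss follows from the document.** A reader might put the cost at 20 to 30 points. That needs roughly 80% interaction power, one cut with about 20% to 50% of children above it, and linearity. Across the assumptions tried, the loss runs from near 0 to about 43 points. This stands in full, so the figures can only be illustrations.

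**Linearity decides the ranking.** If benefit is confined to children beyond a threshold and the cut is placed there, grouping does better. A contrast between at-risk and other children can also be a legitimate question in itself. Both stand in part: no threshold is argued for in the article, and group estimates can still be reported.

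**The link to aim 3 is indirect.** The SDQ is not among that aim's examples, although they are introduced as examples only, and the SDQ is one of just two bases given for subgroups. Nor does the article commit to reading a null subgroup result as absence of moderation; that too would be an inference.

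**Conclusion.** The concern holds in conditional form. Where modification by baseline SDQ is about linear and a single cut is used, grouping keeps about 64% (median) or 49% (top 20%) of the information, and an assumed 80% power falls to about 61% or 50%. The normal distribution, linear gradient, cut and starting power are assumptions; the article supplies none of them. The loss is about 10 points with ordered tertiles, small when power is very high or very low, and turns into a gain if the effect is a true step at the chosen cut.

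This is a cheap improvement to a secondary analysis. A reader might infer that the trial's main conclusion is at risk; it is not, because the primary comparison of arms does not use these subgroups.

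**What to change.** In the Plan of statistical methods, or in the SAP:

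- Make the secondary test of moderation by SDQ a single treatment-by-baseline-SDQ interaction, with the score kept continuous, in the same random-effects model.
- Add a quadratic or spline term for the score and its interaction as a check on linearity.
- Report the intervention effect with its confidence interval at SDQ values chosen in advance, for example values typical of the normal, borderline and abnormal ranges.
- Keep the SDQ subgroup estimates as description, not as the test.

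The cost is one model term and a sentence or two of wording, with no new data. The downside is reliance on approximate linearity, which the check covers in part.

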## Discussion

The aim of this paper is to describe a cluster randomized controlled trial regarding an intervention program designed to promote children’s socio-emotional skills and mental health in a school context. The presented intervention program is built on prior literature and research on the tools and methods on effective interventions and programs. The program integrates methods shown to be effective which in turn are based on thorough intervention development and a pilot study combined with knowledge of educators and clinicians about what will work in the real world environment. The trial presented in this protocol aims to expand our knowledge on the effectiveness regarding the promotion of children’s mental health in European schools via a socio-emotional intervention program using a whole school approach. Specifically, the aim of the presented trial is provide more information on adapting evidence-based methods for diverse cultures and related school settings.
